## Abstract

**Background:**

Long-acting injectable cabotegravir (CAB-LA) is highly effective for HIV pre-exposure prophylaxis (PrEP). However, lactating women have been underrepresented in pharmacokinetic and safety studies despite their elevated risk of HIV acquisition and potential postnatal transmission through breastfeeding. Data on cabotegravir transfer into breast milk and infant exposure remain limited. The Cabotegravir in Mother–Infant Pairs and Lactation Pharmacokinetics (CABMILK) study addresses this evidence gap to inform safe and equitable PrEP delivery within maternal and child health services in Malawi.

**Objectives:**

The primary objective is to quantify cabotegravir transfer into breast milk and estimate infant exposure following maternal use of CAB-LA for PrEP. Secondary objectives are to describe and contextualise infant safety outcomes, including growth, developmental status, and adverse events—among infants whose mothers receive CAB-LA, oral PrEP (tenofovir disoproxil fumarate/emtricitabine), or no PrEP, and to explore maternal factors associated with breast milk drug concentrations.

**Methods:**

CABMILK is an observational pharmacokinetic study nested within two ongoing CAB-LA implementation studies in Malawi. A total of 100 mother–infant pairs will be enrolled: 25 receiving CAB-LA, 25 receiving oral PrEP, and 50 PrEP-naïve. Serial maternal plasma and breast milk samples will be collected to quantify cabotegravir concentrations using validated LC–MS/MS assays and to estimate milk-to-plasma ratios and infant exposure. Infant safety monitoring will include clinical assessments, growth measurements, and developmental evaluation using the Caregiver Reported Early Development Index (CREDI) Short Form over 8 months of follow-up.

**Expected findings:**

This study will provide empirical data on cabotegravir transfer into breast milk, quantify infant exposure, and generate early comparative safety data.

**Conclusions:**

CABMILK will generate essential evidence to guide the safe implementation of CAB-LA among breastfeeding women and inform HIV prevention policy in high-burden settings.

^ These observations support the expectation that CAB concentrations in breast milk are likely to be low, although direct human CAB lactation data remain limited.

Given the prolonged exposure to LAI CAB, with an apparent half-life of around 40 days,
^
9,
14
^ there is a need to establish how much CAB transfers to a breastfeeding infant and its associated safety. In the ongoing PathToScale implementation study in Lilongwe and Blantyre, Malawi, the inclusion of diverse subpopulations, such as pregnant women and lactating mothers, will be prioritised to allow the collection of evidence on the safety and acceptability of CAB for PrEP in various key target subgroups. Additionally, an ongoing effectiveness implementation cluster randomised clinical trial is assessing innovative strategies to increase uptake and retention in care for post-partum women who are breastfeeding and initiating long-acting injectable or oral PrEP (LINK Study in Lilongwe, Malawi). These two implementation studies provide a unique platform to nest a cohort study to understand the breastmilk transfer of CAB to infants and its subsequent safety in these young children. Through the cabotegravir in mother-infant pairs and lactation pharmacokinetics study (CABMILK Study), we aim to address this knowledge gap by determining the extent to which CAB is transferred to the infant through breastmilk, and explore whether CAB breastmilk concentrations, if any, are high enough to cause adverse effects in the infant, and affect growth or neurocognitive development.

## Main and specific objectives of the CABMILK study

The broad objective of the CABMILK Study is:
•To characterise cabotegravir transfer into breastmilk and the resulting infant exposure among breastfeeding women receiving long-acting injectable cabotegravir for HIV pre-exposure prophylaxis, and to describe, in a preliminary, non-inferential manner, the infant safety, growth, and developmental patterns in this group relative to infants whose mothers receive oral PrEP (TDF/FTC) or no PrEP.

The specific aims of the study are:
•To evaluate the extent of cabotegravir transfer into breast milk and determine its pharmacokinetics in infants who are breastfed by mothers receiving long-acting injectable cabotegravir for HIV PrEP.•To describe the pattern of infant safety, growth, and developmental outcomes over eight months of follow-up among infants exposed to cabotegravir through breastmilk, those exposed to oral TDF/FTC through breastmilk, and PrEP-naïve infants, with effect sizes and 95% confidence intervals reported without formal between-group hypothesis testing

## Methodology

### Study design and population

To address the outlined study aims, an observational pharmacokinetic cohort study (
Figure 1), will be conducted in two steps. In the first step, lactating mothers under the PathToScale or LINK studies who choose CABLA for PrEP will be targeted for enrolment in order to profile the extent of breastmilk CAB transfer to the infant following maternal intramuscular CAB administration for PrEP. In the second step, an assessment of the safety outcomes (growth, neuro-cognitive development patterns and incidence of adverse events) in infants exposed to breastmilk CAB compared with those exposed to oral PrEP or PrEP-naïve infants will be made. The CABMILK Study will be nested within two ongoing CAB PrEP studies in Malawi, the PathToScale Study and the LINK Study (
Figure 1). The PathToScale Study aims to assess CAB implementation readiness and outcomes (feasibility, acceptability, appropriateness, adaptation, and fidelity) according to the preliminary national CAB PrEP guidelines in Malawi (currently under development). PathToScale will recruit 9,900 participants into the CAB group and 13,000 participants into the standard of care (oral daily PrEP of the TDF/FTC combination) between January 2024 and December 2026. The LINK Study is an effectiveness implementation cluster randomised clinical trial that is assessing innovative strategies, such as the alignment of PrEP services to routine under-five clinic visits, to increase uptake and retain in-care postpartum women who are breastfeeding and initiating long-acting injectable or oral PrEP.
^
15
^ LINK will randomise 12 clinics in Lilongwe District into two clusters: one with improved innovative strategies for increasing uptake of CAB and oral PrEP and a second cluster of standard care. Combined, both clusters are expected to recruit at least 600 breastfeeding women between 2024 and 2027 (150 at the standard of care sites and 450 at the intervention sites over three years) and follow them up.

**Figure 1. f1:**
[figure not shown]
Study design and follow-up schedule for the CABMILK study. Schematic overview of the CABMILK observational pharmacokinetic cohort study. Lactating mother–infant pairs are enrolled into one of three groups based on their HIV pre-exposure prophylaxis (PrEP) choice: injectable cabotegravir (CAB-LA), oral PrEP (tenofovir disoproxil fumarate/emtricitabine), or no PrEP. The diagram illustrates the expected number per group, timing of PK samples in group A, alongside clinical follow-up visits for safety, growth, and developmental assessments over the eight months follow up.

In the CABMILK Study, three groups of mother-infant pairs will be included as follows: i) 25 mother-infant pairs from a group of lactating mothers who opt to receive long-acting CAB injectable ii) 25 mother-infant pairs from a group of lactating mothers who opt to receive standard oral PrEP comprising tenofovir disoproxil fumarate and emtricitabine, and iii) 50 mother-infant pairs from a group of lactating mothers who chose not to be on oral or injectable PrEP (PrEP unexposed group) (
Figure 1). While this study leverages data collection platforms established by PathToScale and LINK for efficiency, the CABMILK Study independently focuses on evaluating cabotegravir transfer into breast milk and its association with infant safety. The research questions and analyses have been designed to address gaps not explored in the parent studies, ensuring originality and relevance to the local context.

### Study place and setting

The study will be conducted in at least two health facilities in Lilongwe district (Area 18 Health Centre and Kawale Health Centre under the clinical research platform of the University of North Carolina (UNC)-Lilongwe project) where long-acting CAB and oral PrEP are being offered as part of the PathToScale and LINK studies. These have been identified in consultation with the Health Offices in both districts and key implementing partners. The choice of a site has also been made based on the availability of maternity care services at the health facilities. All sites will be expected to contribute towards this study’s total sample size (n=100), depending on the levels of participant recruitment in the parent studies.

### Inclusion and exclusion
*criteria*

*The inclusion criteria of the study are:*

Eligible participants will be breastfeeding mother–infant dyads recruited from health facilities participating in the PathToScale and LINK implementation studies. Inclusion criteria are designed to identify HIV-negative breastfeeding mothers with anticipated or documented exposure to oral or long-acting injectable cabotegravir for HIV pre-exposure prophylaxis (PrEP), while ensuring the feasibility of pharmacokinetic sampling and infant safety follow-up.

Specifically, eligible mothers will be HIV negative, aged 15 years or older and are either: (i) intending receive oral or injectable cabotegravir PrEP under government facilities which maybe PathToScale or LINK studies implementation sites, or (ii) HIV-negative breastfeeding mothers attending postnatal or under-five clinics at participating facilities. Mothers will be expected to be willing and able to comply with all study procedures as described in the Participant Information Leaflet (PIL) and to provide written informed consent for themselves and their infants or assent for participants less than 18 years of age. It will be expected that infants remain within the infant age range at the time of planned mother–infant pharmacokinetic sampling to allow adequate assessment of cabotegravir exposure and safety outcomes. As such enrolment for eligible mother-infant pairs shall occurs from the first week of birth to less than 5 months.

*The exclusion criteria of the study are:*

Exclusion criteria will be applied primarily to protect participant safety and preserve the interpretability of pharmacokinetic measurements. Mother–infant dyads will be excluded if either the mother or infant is receiving concomitant medications known to significantly alter cabotegravir exposure, including rifamycin--based tuberculosis prevention or treatment. Enrolment will be restricted to infants with a birthweight ≥1.5 kg; extremely preterm and clinically unstable neonates are therefore excluded, but otherwise well preterm infants are eligible in order to preserve generalisability to the real-world population receiving CAB-LA under the parent studies. Gestational age at birth will be recorded at enrolment and used as a covariate in analyses. Dyads will also be excluded if the infant has a documented congenital anomaly expected to affect drug disposition or survival. Severe anaemia, defined as haemoglobin concentration < 5 g/dL, will constitute an exclusion criterion. In addition, participants will be excluded if they are found to be concurrently enrolled in another interventional clinical trial, with the exception of the PathToScale or LINK implementation studies.

### Data collection techniques and tools for the CABMILK study

Procedures in the CABMILK study are outlined in
Figure 2 and
Table 1. Data will be collected using case-report forms (CRF) that were developed using open data kit (ODK) platform.

**Figure 2. f2:**
[figure not shown]
Pharmacokinetic sampling schedule for the CABMILK study. Timeline of maternal plasma, breastmilk, and infant dried blood spot (DBS) sample collection used to characterize cabotegravir pharmacokinetics and infant exposure during breastfeeding. The sparse PK sampling visit occurs at month 7 after enrolment, corresponding to the fifth CAB-LA injection, after participants have received four prior injections. This schedule enables estimation of maternal drug concentrations, milk-to-plasma ratios, and infant exposure metrics.

**Table 1. T1:** Schedule of study procedures and sample collection in the CABMILK study.

Visit description											
Visit number	1	2	3	4	5	6	7	8	9	10	Unscheduled
Visit month	0	1	3	5	7	7	7	7	7	8	Any
Visit study time	Pre- dose	Pre- dose	Pre- dose	Pre- dose	Pre-dose (0 hr)	24 hr	Day 7±3	Day 14±3	Day 28±5	Study exit	Sick visit
Screening and enrolment											
Informed consent discussion	x										
Medical and drug history	x										x
Revision of eligibility criteria	x										
ID number assignment	x										
Capillary haemoglobin measurement	x				x						
Group A: Mother-infant pairs on cabotegravir PrEP											
General physical examination	x	x	x	x	x	x	x	x	x	x	x
Recording of current and concomitant medication	x	x	x	x	x	x	x	x	x	x	x
Anthropometric measurements to assess growth ^#^	x	x	x	x	x					x	
Cognitive and neuro-assessment using a validated tool such as MDAT or equivalent	x	x	x	x	x					x	
Adverse events assessment	x	x	x	x	x	x	x	x	x	x	
Maternal venous blood PK sample					x		x				
Mandated breastmilk feeding or record of latest time of feeding*							x				
Maternal breastmilk PK sample					x		x				
Infant capillary blood PK sample					x	x	x	x	x		
Infant feeding patterns and record of any food supplementation	x	x	x	x	x	x	x	x	x	x	x
Groups B & C: Mother-infant pairs in oral PrEP group and PrEP naïve											
General physical examination	x	x	x	x	x					x	x
Recording of current and concomitant medication	x	x	x	x	x					x	x
Anthropometric measurements to assess growth ^#^	x	x	x	x	x					x	
Cognitive and neuro-assessment	x	x	x	x	x					x	
Adverse events assessment	x	x	x	x	x					x	

This table outlines the timing of study visits and procedures for enrolled mother–infant pairs, including maternal clinical assessments, breastmilk and plasma sample collection, infant dried blood spot (DBS) sampling, and safety, growth, and developmental evaluations. Procedures are aligned with maternal cabotegravir dosing schedules and routine follow-up visits.

### Cabotegravir injectable and oral PrEP administration

Long-acting CAB in the parent PathToScale and LINK implementation studies will be administered as a 600 mg intramuscular injection in the ventrogluteal region by a trained provider certified by the MoH on the same day that a client is determined to be eligible. This will be followed by a second injection 1 month after the first and subsequent injections every 2 months until the final injection at eight months. Oral PrEP will be administered as a daily single tablet of 300 mg tenofovir disoproxil fumarate/200 mg emtricitabine. Participants in this group will be followed up until eight months in our study.

### Step 1-
CABMILK study- Cabotegravir maternal, breastmilk and infant pharmacokinetic study

We hypothesise that cabotegravir administered as long-acting PrEP in lactating mothers may be detectable in breast milk and infant plasma, but that the magnitude of infant exposure and its clinical significance remain uncertain. The study is designed to quantify breast milk transfer, estimate infant systemic exposure, and evaluate infant safety. If infant exposure occurs at very low, subtherapeutic concentrations, this could have theoretical implications for resistance in the event of HIV acquisition during breastfeeding; however, it is also possible that transfer is minimal and clinically reassuring and safe. CAB would transfer.

*Cabotegravir pharmacokinetic sampling: maternal plasma, breastmilk, and infant plasma*

25 lactating mothers initiating CAB PrEP within the PathToScale Study or LINK Study will be approached for participation in the study. Since CAB has a half-life of 40 days
^
9,
14
^ it would be expected to attain a steady state in the mother at least after 4 half-lives
^
16
^ (i.e. in the case of CAB, at least 160 days) from the first initial dose. To ensure that we conduct pharmacokinetic sampling of CAB at steady state, we will collect samples for CAB concentrations before the 5th CAB maternal dose (i.e. before the maternal dose at 7 months postpartum).

In mothers, 5 mL of venous blood will be collected using calibrated EDTA tubes. It will be separated in the laboratory to collect plasma and frozen in at least two aliquots at -80 degrees Celsius in readiness for a validated liquid chromatography–tandem mass spectrometry (LC–MS/MS) assay. Breastmilk CAB samples will be paired and collected by manual expression at pre-dose and at the expected time of maternal peak (Cmax), 7 days (±3) post-5th CAB dose. No more than 5 mL of breast milk will be collected in a clear container at each sampling time point. Thereafter, the sample will be frozen in at least two aliquots and stored at -80 degrees Celsius in readiness for cabotegravir assay. Therefore, each mother will contribute two breastmilk and blood samples.

To characterise and profile infant CAB exposure from breastmilk, 200 μL of infant capillary blood will be collected through a finger/heel prick at the expected time of trough- (sample collected before dosing in the mother) and peak (expected Cmax) concentrations at 7 days (±3)
^
17
^ post-dose. The latter will be achieved by aiming to mandate a feed at the expected maternal peak and then sampling 1 hour later or, where mandated feeding is not possible, collecting information on the time of last infant breastfeeding. We will further collect infant capillary blood samples at 24 hours then 7 (±3), 14 (±4) and 28 (±5) days post maternal CAB dosing, resulting in five infant sampling occasions (
Figure 2). The collected blood sample will be applied on two dry blood spot (DBS) filter papers (Whatman 3MM) and left to dry. The DBS filter papers for each participant will be stored, with desiccant, in sealed zipper plastic bags to ensure that they do not pose any potential biological hazards. They will be stored at room temperature at a collaborating institution, the University of North Carolina (UNC)’s laboratory before shipment to assay cabotegravir concentrations. The remaining samples will be archived at Malawi-Liverpool-Wellcome Programme (MLW)’s laboratory in Blantyre.

Ideally, venous plasma samples, as opposed to capillary samples, should also be collected in infants (as in the case of the mother). However, to limit the amount of infant blood sampling volume, a capillary blood sampling matrix has been opted for in the infants.

*Duration of sample storage*

All samples (breast milk and blood) will be collected in duplicate; one backup at the Malawi-Liverpool Wellcome Programme (MLW) laboratory and the other shipped for cabotegravir assay. The maximum period of sample storage at MLW (backup samples) will be five years.

*Assaying cabotegravir concentrations*

Breast milk and blood samples will be shipped to the University of Cape Town’s Division of Clinical Pharmacology Laboratory or the Infectious Diseases Institute Laboratory in Uganda for quantification of cabotegravir concentrations. Samples will be analysed using a validated liquid chromatography–tandem mass spectrometry (LC–MS/MS) assay capable of detecting very low concentrations of cabotegravir in plasma, breast milk, and dried blood spot matrices. The assay has been validated in accordance with international bioanalytical method validation guidelines, including assessment of accuracy, precision, recovery, matrix effects, and analyte stability. The lower limit of quantification (LLOQ) is expected to be in the low ng/mL range, sufficient to detect concentrations anticipated in infant samples. External quality control samples and calibration standards will be included in each analytical run.

Shipment of samples outside Malawi is required because this highly sensitive LC–MS/MS method for cabotegravir is not currently available locally.

*Information on other factors that could impact CAB breastmilk exposure*

Two classes of variable are recognised as potentially affecting cabotegravir concentrations in breastmilk and the resulting infant exposure: (a) infant feeding pattern, and (b) maternal nutritional status. Infant feeding will be captured at every visit using standard feeding indicators (exclusive vs mixed) and the timing and frequency of feeds relative to sampling and will be entered into pharmacokinetic and safety analyses as a time-varying covariate. Maternal pre-injection weight will be measured at baseline and at each dosing visit and evaluated as covariates on cabotegravir apparent clearance and on the milk-to-plasma ratio in the population PK model. We acknowledge as a limitation that the study does not directly measure milk fat fraction or detailed maternal dietary intake, and therefore cannot fully resolve any indirect effect of maternal diet on infant cabotegravir exposure.

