### Data analysis

Data will be analysed using either STATA or R.
Table 2 outlines the planned data analyses stratified by the specific objectives of the study. Infant age at every sampling occasion and at every safety and developmental assessment will be recorded to the day. Both postnatal age (PNA) and postmenstrual age (PMA = gestational age at birth + PNA) will be derived for each timepoint and treated as time-varying variables. The population pharmacokinetic model (NONMEM/Monolix) will incorporate, as fixed structural features, allometric size scaling (exponent 0.75 on apparent clearance, 1 on volume of distribution) and a sigmoidal maturation function on apparent clearance, with PMA50 and the Hill coefficient set to published values for UGT1A1 ontogeny rather than estimated from this small cohort. Residual covariate effects of PNA, weight, sex, and feeding pattern will then be tested empirically. To probe the robustness of the maturation assumption, we will conduct a pre-specified sensitivity analysis re-fitting the model with at least one alternative published UGT1A1 ontogeny parameter set (1) and report the resulting impact on individual exposure estimates. Relative infant dose (RID) will be reported overall and by infant-age stratum (<9 months and 9–<12 months). Comparative growth and developmental analyses will use WHO z-scores and age-adjusted CREDI scores; longitudinal mixed-effects models will include infant age at measurement as a continuous covariate. Because exposure groups are self-selected, all comparative analyses are observational and exploratory. Primary safety results will be descriptive: counts, proportions with exact 95% confidence intervals, incidence rates, and Kaplan–Meier curves, without group-comparison p-values. Longitudinal growth and CREDI outcomes will be analysed with mixed-effects models adjusting for a minimal pre-specified set of covariates: infant age at measurement, infant sex, and site. Formal between-group inference for safety is deferred to other larger PK studies. Where feasible, we will perform sensitivity analyses to reduce imbalance, recognising limitations due to our sample size.

**Table 2. T2:** Planned data analyses aligned with study objectives in the CABMILK study.

Objective	Data analysis	Outcome

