To profile the extent of CAB transfer in breast milk and determine its pharmacokinetics in infants whose mothers receive long-acting injectable cabotegravir for HIV preexposure prophylaxis (PrEP).	We will use non-linear mixed effects models to determine the compartmental pharmacokinetics of CAB from maternal plasma to breast milk to infant plasma. We will first calculate the milk: plasma ratio to determine the average milk CAB concentration compared with the average maternal plasma concentration. Second, we will utilise individual predicted infant CAB concentrations to calculate infant overall exposure (AUC0-∞) and estimate CAB infant half-life as well as elimination rate constant. Third, we will estimate the CAB dose ingested by each infant, through breast milk, relative to the maternal dose; the relative infant dose (RID). ^ 25 ^ This RID will allow us to determine the extent of CAB breast milk exposure that would result in attained concentrations in the infant’s blood that are above or below the protein-adjusted IC90 of 0.166 μg/mL. ^ 26 ^	CAB transfer to the infant through breast milk, and profile the attained infant concentrations.
To determine the association of breast milk CAB exposure and infant safety outcomes (growth pattern, neuro-cognitive development, and incidence of adverse events).	Firstly, mean anthropometric indices (weight-for-height, height-for-age, head circumference-for-age) will be compared across three groups using independent t-tests. Secondly, adverse events (overall morbidity) by the end of follow-up will be compared across the three groups using Chi-squared tests. Age-standardised CREDI summary scores (z-scores) analysed as continuous outcomes, reported as adjusted mean differences with 95% confidence intervalsUsing linear regression, we will assess whether breast milk CAB concentrations predict growth patterns and morbidity, adjusting for infant age, sex socio-economic status, birth weight and gestation age at birth. Random effects models will account for intra- and interindividual variability in repeated measurements. Exploring this analysis may inform algorithms for monitoring CAB safety signals in infants. These algorithms could be validated in larger studies and incorporated into routine practice for early detection of CAB-related risks in infants.	Impact of CAB breast milk exposure on infant growth and neurocognitive development in comparison to the standard daily oral PrEP.

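### Infant feeding is promised as a time-varying covariate in the safety analyses, but Table 1 schedules the feeding record only for the CAB-LA group and no stated safety model includes it

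*Protocol article*

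**What the plan says.** Under Step 1, the subsection on other factors that could affect CAB breast milk exposure states: "Infant feeding will be captured at every visit using standard feeding indicators (exclusive vs mixed", together with the timing and frequency of feeds around sampling. It then says that feeding "will be entered into pharmacokinetic and safety analyses as a time-varying covariate". No study group is named. The Limitations section makes the same commitment, again without restricting it to one group, when it discusses influences on infant exposure.

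Table 1 is the visit schedule. Its block headed "Group A: Mother-infant pairs on cabotegravir PrEP" ends with the row "Infant feeding patterns and record of any food supplementation", marked at all ten scheduled visits and at the unscheduled visit. The next block, "Groups B & C: Mother-infant pairs in oral PrEP group and PrEP naïve", has five rows: physical examination, medication, anthropometry, cognitive and neuro-assessment, and adverse events. None concerns feeding.

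The Data analysis section describes the mixed models for growth and CREDI as "adjusting for a minimal pre-specified set of covariates: infant age at measurement, infant sex, and site". Table 2 describes a regression of growth and morbidity on breast milk CAB concentration, "adjusting for infant age, sex socio-economic status, birth weight and gestation age at birth". Feeding pattern is named as a model covariate only for the population pharmacokinetic model.

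**The concern.** Three parts of the plan do not fit together: what is promised (feeding used in the safety analyses), what is scheduled (feeding recorded in one group of three) and what is modelled (no safety model with feeding in it).

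Infant feeding may differ between self-selected groups and may bear on growth and illness, so a reader of the three-group comparison will want to see it side by side. Under Table 1 that display cannot be made, and nor can any feeding-adjusted group comparison. The Limitations section cites longitudinal capture of feeding as part of its answer to a recognised weakness. If the safety models never contain feeding, that answer does not hold for them.

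Timing matters too. The Study status section says that recruitment began in September 2025 and continues. Feeding not recorded at a visit is hard to reconstruct afterwards.

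**Working it through.** The plan gives no figure on this point, so the check is a comparison of sections and a count.

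**Inputs**
- Group sizes: 25 CAB-LA, 25 oral PrEP, 50 PrEP-naïve (sample size section).
- Visits: ten in the CAB-LA group and six in each comparison group (Step 2). Table 1 agrees: the comparison groups' growth and adverse-event rows are marked at visits 1 to 5 and 10.
- Feeding row: CAB-LA block only, all ten scheduled visits (Table 1).

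**Pairs with a scheduled feeding record**
- CAB-LA: 25 of 25.
- Comparison groups: 0 of 25 + 50 = 75.
- Overall: 25 of 100 (25%).

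**Pair-visits at the six common visits**
- Total: 100 × 6 = 600.
- With feeding scheduled: 25 × 6 = 150 (25%).
- Without: 75 × 6 = 450 (75%).

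The four additional pharmacokinetic visits bring the CAB-LA total to 25 × 10 = 250 visits with feeding, but these have no counterpart in the other groups and add nothing to a comparison.

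**Is feeding in a stated model?**

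| Analysis | Covariates stated | Feeding included? |
|---|---|---|
| Population PK (Data analysis) | postnatal age, weight, sex and feeding, tested after fixed size and maturation terms | yes |
| Growth and CREDI mixed models (Data analysis) | age, sex, site | no |
| Milk concentration against growth and morbidity (Table 2) | age, sex, socio-economic status, birth weight, gestation | no |
| Adverse events (Data analysis) | descriptive, no covariates | not applicable |

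**Consequence.** If feeding were put into a three-group model fitted to the records that have it, only the CAB-LA group would remain and no group contrast could be estimated. If feeding is left out, as the stated sets imply, the commitment to use it in the safety analyses is not met.

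**After the fix.** With the row added at the six existing visits, feeding is scheduled for 100 of 100 pairs and 600 of 600 common pair-visits.

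**The case against.** The strongest reply is that the commitment was never meant to cover all groups. It sits in a pharmacokinetic subsection and concerns feeds relative to sampling, and only the CAB-LA group is sampled. Its every-visit wording matches the CAB-LA row of Table 1. On this reading the safety analyses in question are the Table 2 regression on milk CAB concentration, which only CAB-LA pairs can inform. The reading is fair, and it would reconcile the text with Table 1. It does not reconcile it with Table 2, because that regression also omits feeding. The wording is also unrestricted in both places where it appears.

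A second reply is that feeding may in fact be recorded in every group and the row was dropped from a condensed table. The case report forms and the analysis plan are said to be available but are not shown here, so this is possible. Step 2 does say that the comparison groups have the same visits and safety assessments, but it does not name feeding among them. Table 1 repeats other shared rows in the comparison block, so the missing row does not look like shorthand.

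A third reply is that the comparisons are exploratory and non-inferential, with residual confounding acknowledged. That stands, and it limits the weight of the point.

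**Conclusion.** The inconsistency is real and worth correcting now. Under Table 1 as printed, 75 of 100 pairs and 450 of 600 common pair-visits have no scheduled feeding record, and no stated safety model contains feeding. The count assumes that Table 1 is the operative schedule; if the forms already collect feeding in all groups, the defect reduces to the table and the covariate lists.

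Three stronger conclusions might be inferred, and the documents do not support them:
- **That the planned three-group model would lose the comparison groups.** The stated growth and CREDI model has age, sex and site only, so it drops no records. The loss arises only if feeding is added without being collected.
- **That feeding is certain to be unavailable for 75 infants.** The text names no group, so the supportable statement is that Table 1 does not schedule it.
- **That adjusting for current feeding would bias an adverse-event comparison because illness changes feeding.** The Data analysis section reports adverse events descriptively, and the only covariate-adjusted morbidity analysis, in Table 2, does not include feeding.

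The primary pharmacokinetic objective is untouched: feeding is scheduled for the CAB-LA group and named in that model.

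**What to change.** - **Table 1:** add the feeding and supplementation row to the oral PrEP and PrEP-naïve block at visits 1 to 5 and 10. If the forms already collect it, correct the table only.
- **Data analysis:** keep time-varying feeding in the population PK model. Keep age, sex and site as the primary set for the growth and CREDI models, and name feeding as a sensitivity adjustment there. State which visit's feeding value is used; that choice is the team's.
- **Step 1 subsection, Table 2 and Limitations:** reword so that all three say the same about which groups have feeding recorded and which analyses use it.

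The cost is one short question, already scheduled for the CAB-LA group, at visits that take place anyway, plus a small change to the documents. Comparison-group infants already seen may lack earlier records. The number affected should be reported, and the sensitivity analysis should state how those visits are handled.
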